### Sample size calculation

The sample size was calculated based on the primary outcome, sputum wet weight, using a non-inferiority design. A non-inferiority margin of 1.5 g was prespecified, as justified above. Variability estimates were obtained from a preliminary pilot study, which indicated a within-subject standard deviation of approximately *σ* g for wet sputum weight following airway clearance interventions.

Assuming a true mean difference of 0 g between NNPO and OPEP, a one-sided significance level (*α*) of 0.025, and 80% power, a minimum of 38 participants was required to demonstrate non-inferiority in this crossover study. To allow for potential dropouts or incomplete data, the target sample size was increased to 42 participants.

## Statistical analysis

All statistical analyses will be performed using R software (version 4.3; R Foundation for Statistical Computing, Vienna, Austria). Normality of continuous variables will be assessed using the Shapiro–Wilk test. Normally distributed variables will be presented as mean ± standard deviation (SD), while non-normally distributed variables will be reported as median (interquartile range, IQR). Categorical variables will be summarized as counts and percentages.

Between-treatment differences in wet sputum weight will be analyzed using linear mixed-effects models (LMMs), with treatment group as a fixed effect and participant as a random effect. In the absence of a statistically significant difference, a non-inferiority analysis will be performed comparing NNPO therapy with OPEP therapy. The non-inferiority margin is set at 1.5 g. As no established margin exists for short-term wet sputum weight, this threshold was determined *a priori* based on evidence suggesting a clinically meaningful 24-h sputum weight change of approximately 6.4 g following airway clearance interventions (16), combined with pilot data demonstrating minimal between-treatment differences. Non-inferiority will be concluded if the lower bound of the 95% confidence interval (CI) for the NNPO–OPEP difference exceeds −1.5 g.

Lung function parameters and oxygenation (SpO₂/FiO₂) will also be analyzed using LMMs to assess pre–post intervention changes and treatment-by-time interactions. Change scores (*Δ*) will be calculated and compared between interventions.

Patient-reported outcomes, including perceived efficacy and comfort, will be compared using independent-samples t-tests or Mann–Whitney U tests, as appropriate. All statistical tests will be two-sided unless otherwise specified. A *p* value < 0.05 will be considered statistically significant, except for the non-inferiority analysis of wet sputum weight, which will use a one-sided significance level of 0.025.

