### Trial design

This prospective, multicenter, randomized, crossover, non-inferiority trial aims to evaluate the efficacy of a novel airway clearance technique, nasal negative pressure oscillatory (NNPO) therapy, in hospitalized patients. The protocol is developed and reported in accordance with the SPIRIT 2025 guidelines (15). To minimize inter-individual variability in sputum production and airway clearance capacity, a self-controlled crossover design is employed, with each participant receiving both interventions and serving as their own control. NNPO therapy is compared with conventional airway clearance using oscillatory positive expiratory pressure (OPEP).

The study is conducted over a continuous 4-day intervention period. Participants receive one intervention on Days 1 and 3 and the alternate intervention on Days 2 and 4. Two treatment sequences are predefined: Sequence A, in which NNPO is administered on Day 1 followed by OPEP on Day 2, and Sequence B, in which OPEP is administered on Day 1 followed by NNPO on Day 2. The same intervention sequence is repeated on Days 3 and 4 to enhance the reliability of treatment comparisons. Allocation to Sequence A or Sequence B is performed using a computer-generated randomization schedule (Figure 1).

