### Outcomes and assessment schedule

The primary outcome was sputum wet weight, collected during each treatment session and for up to 30 min after session completion. Sputum was collected into pre-weighed, sealed sterile containers and immediately weighed using a calibrated electronic scale. Collection was performed using a standardized procedure under the supervision of study personnel throughout the airway clearance process. During collection, participants were instructed to avoid swallowing sputum when present and to expectorate it promptly for collection. Study personnel made real-time judgments based on the pattern of expectoration and avoided collecting secretions following throat clearing or intentional saliva generation. For participants with viscous oral secretions that might increase the risk of saliva contamination, mouth rinsing with water was permitted prior to treatment to reduce oral contamination.

Secondary outcomes include: (1) Lung function—FEV₁, FVC, FEV₁/FVC, MEF₇₅, MEF₅₀, MEF₂₅, and MMEF₇₅/₂₅—measured before and 30 min after each daily treatment session. Lung function parameters were assessed using a respiratory rehabilitation device (PE100, e-Linkcare Meditech Co., Ltd.); (2) peripheral oxygen saturation (SpO₂/FiO₂) measured at rest before treatment, during the final minute of each session, and 30 min post-treatment; (3) patient-reported treatment efficacy and comfort assessed using 10-cm visual analogue scales after completion of all treatment days; and (4) the incidence of adverse events during or immediately after each session (Table 2).

**Table 2 tab2:** Assessment schedule for primary and secondary outcomes.

Outcome	Time points of assessment
Sputum wet weight (g)	Collected during each treatment session and up to 30 min post-intervention
Lung function (FEV1, FVC, FEV1/FVC, MEF75, MEF50, MEF25, MMEF75/25)	Measured immediately before each daily treatment session and 30 min after completion
Peripheral oxygen saturation (SpO₂/FiO₂)	Recorded at baseline (pre-treatment), during the final minute of the session, and 30 min post-treatment
Patient-reported treatment efficacy (VAS 0–10)	Assessed after completion of all daily treatment sessions
Patient-reported comfort (VAS 0–10)	Assessed after completion of all daily treatment sessions
Adverse events	Monitored during and immediately following each treatment session

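### Read as a random intercept, the primary model lets no participant differ in response to the two devices, so its non-inferiority interval has the wrong width if they do

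*Protocol article*

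**What the plan says.** Under Trial design the article gives each device twice per person: "Participants receive one intervention on Days 1 and 3 and the alternate intervention on Days 2 and 4". The purpose of the repeat is stated: "The same intervention sequence is repeated on Days 3 and 4 to enhance the reliability of treatment comparisons". Sputum is weighed at every session (Outcomes and assessment schedule), which gives four values per participant, two per device.

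The Statistical analysis section fixes the primary model: "Between-treatment differences in wet sputum weight will be analyzed using linear mixed-effects models (LMMs), with treatment group as a fixed effect". The full clause on the effects reads "with treatment group as a fixed effect and participant as a random effect". It states no participant-by-treatment term, no averaging of sessions within device, no robust variance and no day or period term. The decision comes from this model's 95% confidence interval for NNPO minus OPEP: "The non-inferiority margin is set at 1.5 g", and the lower limit must lie above −1.5 g, in a test "which will use a one-sided significance level of 0.025".

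The Limitations section says that sputum volume may decline over the treatment course.

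**The concern.** With two sessions per device, the data contain two kinds of within-person variation. One is session-to-session noise. The other is the extent to which a given person does better on one device than on the other. The average device effect across patients should be judged against both.

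A random intercept removes only the person's overall sputum level. It assumes that the device difference is identical in everyone and pools all remaining variation into one residual, with about 3n degrees of freedom instead of about n. If people do differ, a person's two replicate differences are correlated and the model counts them as independent evidence. The standard error is then too small and the lower confidence limit too high. In a non-inferiority trial that error favours the new device.

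Varying response is plausible on the article's own rationale. The Introduction says NNPO depends little on patient effort whereas OPEP needs active exhalation. The Discussion expects NNPO to be useful especially for patients who are tired or find conventional techniques difficult.

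**Working it through.** **Inputs from the article.** Two sessions per device per person; treatment fixed and participant random; margin 1.5 g; one-sided alpha 0.025; true difference 0 g; 80% power; minimum 38 participants, target 42.

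**The plan's own figure.** The 38 cannot be reproduced, because the within-subject SD is printed only as the symbol σ. Solved backwards, the SD of a participant's difference is 1.5 × sqrt(38)/(1.960 + 0.842) = 3.30 g. That corresponds to a session SD of 3.30/sqrt(2) = 2.33 g if the calculation used one session per device, or 3.30 g if it used the mean of two sessions with no participant-by-device variance.

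**Notation (assumed quantities).** s_e is the session SD, s_D the SD of the person-specific device difference, and r = s_D/s_e.

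**Standard error without a day trend.**
- True variance of the mean difference: (s_e² + s_D²)/n.
- Variance used by the intercept-only model: about (s_e² + s_D²/3)/n, because only one of the three within-person degrees of freedom carries s_D². Residual degrees of freedom are 3 × 38 − 1 = 113, against 38 − 1 = 37 for one contrast per participant.
- Model SE / true SE = sqrt((1 + r²/3)/(1 + r²)); one-sided error = Φ(−1.96 × ratio).

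| r | SE ratio | one-sided error |
|---|---|---|
| 0 | 1.00 | 2.5% |
| 0.5 | sqrt(1.0833/1.25) = 0.931 | 3.4% |
| 0.75 | sqrt(1.1875/1.5625) = 0.872 | 4.4% |
| 1 | sqrt(1.3333/2) = 0.816 | 5.5% |

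Simulation with n = 38 and a true difference of −1.5 g agrees, to within a few tenths of a percentage point. Using 42 participants changes nothing material.

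**Adding a common day trend to the model as written.** Suppose sputum falls by δ g per day. Within a person, the linear trend adds 1.5² + 0.5² + 0.5² + 1.5² = 5 times δ² to the sum of squares. With balanced sequences it does not bias the device difference, so it goes into the residual as about 5δ²/3. The ratio becomes sqrt((1 + r²/3 + 5δ²/(3s_e²))/(1 + r²)). With s_e = 2.33 g (s_e² = 5.43):
- δ = 1 g/day adds 1.667/5.43 = 0.307. At r = 0.5 the ratio is sqrt(1.390/1.25) = 1.05, error 1.9%. At r = 1 it is sqrt(1.640/2) = 0.91, error 3.8%.
- δ = 2 g/day adds 6.667/5.43 = 1.228. At r = 0.5 the ratio is sqrt(2.311/1.25) = 1.36, error 0.4%. At r = 1 it is sqrt(2.561/2) = 1.13, error 1.3%.

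The two faults cancel where 5δ²/3 = (2/3)s_D², that is δ = 0.632 × r × s_e: 0.74 g/day at r = 0.5 and 1.47 g/day at r = 1.

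**After correction.** Using one mean NNPO minus mean OPEP contrast per participant, with sequence as a factor, simulated error stayed between 2.4% and 2.7% in every scenario. Adding only a day effect to the intercept model brings the error back to the no-trend figures in the table, about 3.4% at r = 0.5 and 5.5% at r = 1.

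**The case against.** The strongest reply is that the size, and even the direction, of the error is not known. A reader might infer that the planned interval is too narrow and that false non-inferiority will exceed 2.5%. The article does not support that. It gives no participant-by-device variance, and at zero variance there is no error. The model as written has no day term, so the decline in sputum that the article itself anticipates can make the interval too wide. This objection stands, and the conclusion is conditional because of it. It is no defence of the model, since the offset depends on an uncontrolled trend and disappears once day is modelled.

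Second, the text says participant is a random effect; it does not say intercept only, and a fuller analysis plan could contain a random treatment effect. That is possible. But the random effect is stated, not left open, and its ordinary reading is an intercept. If a fuller plan differs, the article's wording needs correcting.

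Third, r = 1 is a large value. With s_e between 2.33 and 3.30 g it implies person-specific differences with an SD well above the 1.5 g margin. Even with equal devices on average, Φ(−1.5/2.33) = 26% to Φ(−1.5/3.30) = 32% of patients would lose more than 1.5 g on NNPO. The excess at r = 0.5, about one percentage point, is modest.

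Fourth, the Introduction speaks of heterogeneity in the effect of airway clearance generally. It makes a varying device difference plausible but neither predicts it nor gives its size.

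**Conclusion.** The point holds conditionally. Read as a random intercept, the stated primary model fixes at zero a variance that this replicated crossover is able to estimate, and it takes the non-inferiority decision from the resulting interval. If responses vary and no day trend is left in the residual, the one-sided error is about 3.4% to 5.5% for r from 0.5 to 1, against 2.5%. If responses do not vary, it is correct.

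For the model exactly as written, without a day term, the interval may be too narrow or too wide: with s_e = 2.33 g, the error ranges from 0.4% (r = 0.5, fall of 2 g/day) to 5.5% (r = 1, no fall). The values of r, the daily fall and the session SD are all assumptions. What is established is that the interval's coverage depends on two quantities the model ignores. The correction is worth making because it is cheap and held the nominal level in every scenario tried; the trial is not shown to have an inflated error rate.

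**What to change.** In the primary model, add a participant-by-treatment random term (equivalently, a random treatment effect per participant) and a fixed effect for day, with Kenward-Roger or Satterthwaite degrees of freedom. Make both changes together, since adding day alone removes the accidental offset and leaves the narrow interval.

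With complete data this matches an analysis of each participant's mean NNPO minus mean OPEP difference with sequence as a factor, which serves as a simple check. The mixed model should stay primary, because the section on missing data relies on it for incomplete records, and the paired contrast loses anyone without sessions on both devices.

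The cost is not wording alone. The interval widens and power falls if responses differ. If 38 was sized on the mean of two sessions (s_e = 3.30 g), approximate power is Φ(1.5 × sqrt(38)/(3.30 × sqrt(1 + r²)) − 1.96): 80% at r = 0, 71% at r = 0.5 and 51% at r = 1. Simulation with t-based limits gives 49% at r = 1, against about 64% for the intercept-only model, so part of the loss comes from the variation itself. If 38 was sized on one session per device (s_e = 2.33 g), the second session gives slack and power returns to about 80% only at r = 1. Stating σ as a number, and the design it refers to, would settle which applies.

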### Randomization and blinding

Randomization was performed using a computer-generated random sequence, which assigned participants to one of two intervention sequences (NNPO first or OPEP first) in a 1:1 ratio. Allocation was concealed using sealed, opaque envelopes prepared by an independent researcher not involved in participant recruitment, intervention delivery, or outcome assessment. Due to the nature of the interventions, participants and treating physiotherapists were not blinded. However, outcome assessors and data analysts were blinded to treatment allocation throughout the study.

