### Washout considerations

A formal washout period will not be incorporated in this study because hospitalized patients with acute exacerbation of bronchiectasis may experience rapid changes in airway secretion burden and clinical status over a short period. In addition, suspending airway clearance during a washout period would be unethical, as secretion clearance is necessary in this patient population, making a prolonged washout period impractical. However, to minimize potential carryover effects, each intervention will be performed on a separate day.

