### Limitations

Limitations include the short intervention period, which precludes assessment of long-term outcomes such as exacerbation recurrence or hospital stay, and the inability to blind participants or therapists. Nonetheless, the use of objective primary outcomes and standardized protocols is expected to minimize bias. Overall, this study will provide high-quality evidence on the short-term efficacy and safety of NNPO and inform evidence-based, individualized airway clearance strategies in hospitalized patients with acute bronchiectasis exacerbations.

In addition, some anticholinergic agents such as ipratropium bromide have been suggested to reduce bronchial secretions (20), which could theoretically influence sputum volume, as well as by the natural clinical course during treatment, in which sputum volume may gradually decrease over time. From an ethical and practical perspective, it was neither feasible nor appropriate to restrict or modify clinically indicated medications in hospitalized patients, and such variability therefore reflects real-world clinical practice. To mitigate the potential bias introduced by these unavoidable factors, this study employed a randomized crossover design, allowing each participant to serve as their own control, focused on sputum expectoration following a single treatment session, and conducted all interventions and assessments at a fixed time each morning. Nevertheless, residual confounding related to concurrent treatments cannot be completely excluded and is acknowledged as a limitation of the study.

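### The primary mixed model has no study-day term, so any common day-to-day trend in sputum widens the non-inferiority interval and costs power

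*Protocol article*

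**What the plan says.** All references are to the protocol article.

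- **Statistical analysis** gives the primary model as a linear mixed-effects model "with treatment group as a fixed effect and participant as a random effect". No day or period term is named. On the decision rule it says: "The non-inferiority margin is set at 1.5 g". The lower bound of the 95% confidence interval for NNPO minus OPEP must exceed −1.5 g; this is the analysis "which will use a one-sided significance level of 0.025".
- **Trial design** sets the schedule: "Participants receive one intervention on Days 1 and 3 and the alternate intervention on Days 2 and 4". The orders are therefore NNPO-OPEP-NNPO-OPEP (Sequence A) and its mirror image (Sequence B).
- **Randomization and blinding** says that the computer-generated list "assigned participants to one of two intervention sequences (NNPO first or OPEP first) in a 1:1 ratio".
- **Washout considerations** says these patients "may experience rapid changes in airway secretion burden and clinical status over a short period".
- **Limitations** refers to the natural clinical course, "in which sputum volume may gradually decrease over time". As mitigation it says "this study employed a randomized crossover design, allowing each participant to serve as their own control", and adds single-session outcomes and a fixed morning time. No model term is offered for the trend.

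**The concern.** Using each participant as their own control removes differences between people. It does not remove a change from one day to the next that all participants share. In a crossover that change is handled by balance between sequences, which protects the point estimate, and by a period term in the model, which protects the standard error. The design supplies the first and the stated model omits the second.

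The article names both the alternating four-day schedule and a possible fall in sputum, and it spells out the model's effects. The omission is therefore in the written model and is not simply a detail left to an unseen analysis plan. At stake is the width of the interval on which non-inferiority rests, in a trial whose minimum of 38 was set for 80% power. To a lesser degree, so is the protection of the estimate against unequal sequences or lost days.

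**Working it through.** **Inputs from the article.** Margin 1.5 g, one-sided alpha 0.025, power 80%, true difference 0 g, minimum 38 participants, target 42; four sessions per participant, two per treatment.

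**Inputs not given, so assumed.** The within-subject SD is printed only as a symbol, and no size of trend is stated. I take declines of b = 0.5, 1, 1.5 and 2 g/day, that is 1.5 to 6 g from Day 1 to Day 4.

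**1. The planned figure.** N = ((1.96 + 0.84) × SD_diff / 1.5)² cannot be run forward without the SD. Solved back from N = 38, SD_diff = 1.5 × √38 / 2.80 = 3.30 g. There are two readings:
- If both sessions per treatment are averaged, the per-person contrast has variance σ²/2 + σ²/2 = σ², so σ = 3.30 g.
- If one pair per person was assumed, the variance is 2σ², so σ = 3.30/√2 = 2.33 g.

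**2. Effect on the estimate.** With a decline of b g/day, NNPO falls one day before OPEP in Sequence A, so the within-person contrast is τ + b. In Sequence B it is τ − b. The model without day estimates τ + b(nA − nB)/N.
- Equal sequences, complete data: exactly τ.
- 22:16 split: the shift is 6/38 × b = 0.158b, so 0.16 g at 1 g/day and 0.32 g at 2 g/day (11% and 21% of the margin). It favours NNPO when Sequence A is larger and OPEP when Sequence B is larger.
- Missing days: someone with Days 1 to 3 only has one treatment on Days 1 and 3 (mean day 2) and the other on Day 2, so the contrast carries no shift. That person no longer offsets a complete participant in the other sequence.

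**3. Effect on the error.** Around each person's mean, a linear trend over four days has sum of squares b²(1.5² + 0.5² + 0.5² + 1.5²) = 5b², spread over 3 within-person degrees of freedom. The residual variance becomes σ² + 5b²/3, and SE = √((σ² + 5b²/3)/N). With balanced sequences the true sampling SD of the estimate stays at σ/√N, so power ≈ Φ((1.5 − 1.96 × SE)/(σ/√N)).

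σ = 3.30 g, N = 38, σ/√N = 0.535 g:

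| b (g/day) | residual variance | SE (g) | power, no day term |
|---|---|---|---|
| 0 | 10.89 | 0.535 | 80% |
| 0.5 | 11.31 | 0.545 | 78–79% |
| 1 | 12.56 | 0.575 | about 76% |
| 1.5 | 14.64 | 0.621 | 70% |
| 2 | 17.56 | 0.680 | 62% |

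Simulation agrees within a point or two (74 to 76% at b = 1). With a categorical day term, simulated power is about 78 to 80% at every trend.

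σ = 2.33 g, N = 38: power without a day term falls from about 97% to about 94–96% at b = 1 (SE 0.432 g) and 85% at b = 2 (SE 0.564 g).

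**4. False claims of non-inferiority.** In simulation with balanced sequences and σ = 3.30 g, one-sided error falls to about 1.4% at b = 1 and 0.7% at b = 2. Averaged over simple randomisation it is 2.3%, 2.1%, 1.8% and 1.6% at b = 0.5, 1, 1.5 and 2. Only an unfavourable split goes above nominal: about 3.3% at 22:16 (NNPO-first larger) and 1 g/day.

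**The case against.** The best defence is that the design already does the important work. With 1:1 mirror-image sequences and complete data the trend cancels from the estimate, and what remains makes the test conservative. This stands, and it sets the severity.

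Other points that stand:
- **The loss may be small.** At 0.5 g/day it is a point or two of power. If σ is 2.33 g, power stays above the planned 80% at every trend tried. If all 42 complete and σ = 3.30 g, power at 1 g/day is about 79%. A pilot SD might already contain day-to-day drift; the article does not say.
- **The article says sputum may decrease**, not that a fall over the four days is expected. The rapid changes it mentions have no stated direction.
- **The crossover is not its only safeguard**, since single-session outcomes and a fixed hour are also listed. Neither removes a trend across days.

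Some stronger readings are tempting but not supported. A reader might infer that the treatment estimate is biased; averaged over randomisation it is not. A reader might infer that a serious imbalance is likely. A difference of 6 or more has probability 44% at N = 42 under simple randomisation, but the article does not state simple randomisation, and blocking is a detail that a condensed article often omits. A reader might also count the missing sequence term as a cause; a sequence term leaves the within-person contrast unchanged. Lastly, a reader might extend the point to lung function and oxygenation. Those analyses use pre-post changes around each session, so drift in level is largely differenced out.

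None of this answers the error argument: the standard error is inflated whenever there is a common trend, however well balanced the trial.

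**Conclusion.** The point holds as a loss of precision. As written, the primary model puts any common day trend into the residual, and the non-inferiority interval is wider than the data warrant. The size depends on two quantities that the article does not give. At σ = 3.30 g and N = 38, power drops from about 80% by a point or two at 0.5 g/day and to about 62% at 2 g/day. At σ = 2.33 g the trial keeps at least about 85% up to 2 g/day.

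Protection of the estimate against chance imbalance and missing days is a second, smaller gain. The documents do not support a claim that the model will produce false non-inferiority or a systematically biased difference. This is a should-fix.

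**What to change.** Add study day to the primary model as a four-level categorical fixed effect, keep participant as a random effect, and take the NNPO minus OPEP confidence interval from that model. A sequence term is optional and conventional.

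The change is one of wording, since the day of every session is already known. It uses three degrees of freedom: with 38 complete participants, 38 × 3 − 1 = 113 within-person residual degrees of freedom become 110. If there is no trend, power is essentially unchanged, at about 79% with or without the term when σ = 3.30 g. The change should be recorded before any comparison by treatment is seen, so that it cannot look data-driven.

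### The non-inferiority interval comes from a model that is valid only if all four days are equally correlated within a participant; the documents do not show whether its error would be too wide or too narrow

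*Protocol article*

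**What the plan says.** The Statistical analysis section of the protocol article specifies a linear mixed-effects model for wet sputum weight, "with treatment group as a fixed effect and participant as a random effect". It names no day or period term and no residual covariance. The decision rule follows in the same section: "Non-inferiority will be concluded if the lower bound of the 95% confidence interval (CI) for the NNPO–OPEP difference exceeds −1.5 g".

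Trial design sets the layout: "Participants receive one intervention on Days 1 and 3 and the alternate intervention on Days 2 and 4". Each participant therefore follows NNPO–OPEP–NNPO–OPEP or the mirror sequence on four consecutive days.

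Two other sections bear on how the days relate to each other. Washout considerations says that these patients "may experience rapid changes in airway secretion burden and clinical status over a short period" and gives this as a reason for having no washout. Limitations describes a natural course "in which sputum volume may gradually decrease over time".

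**The concern.** A participant random effect with independent residuals gives Days 1 and 2 the same correlation as Days 1 and 4. If participants recover at different speeds, neighbouring days will be more alike than distant ones, and a common day effect would not remove that. If participants respond differently to the two devices, the two days on the same device will be more alike. If a productive session leaves less to clear the next morning, neighbouring days may even be negatively correlated. None of these patterns is equal correlation.

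The treatment contrast is built from alternating days, so its true variance depends on exactly these patterns. The non-inferiority decision rests on one confidence limit. If the standard error is wrong, either a truly non-inferior device fails too often, or an inferior one passes more often than the stated 2.5%.

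**Working it through.** **Inputs from the protocol article.** Margin 1.5 g, true difference 0 g, one-sided α 0.025, power 80%, 38 evaluable and 42 targeted participants (Sample size calculation); alternating layout (Trial design). The within-subject SD is printed only as a symbol: "which indicated a within-subject standard deviation of approximately *σ* g for wet sputum weight". No between-day correlation is given. All correlations and variance ratios below are assumptions.

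**The plan's own figure.** The 38 cannot be reproduced without σ. Solving backwards, N = (SD_d × 2.802 / 1.5)², where 2.802 = 1.960 + 0.842. N = 38 therefore implies SD_d = 1.5 × √38 / 2.802 = 3.30 g for the per-participant NNPO–OPEP difference. Each scenario is scaled to this SD_d, so that a correct interval has 80% power at 38.

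**Variance of the contrast.** Take the mean of the two NNPO days minus the mean of the two OPEP days, residual variance σ², and correlations r1, r2, r3 at lags of 1, 2 and 3 days.

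- True variance: σ²[1 + (−3r1 + 2r2 − r3)/2]
- Variance reported under equal correlation: σ²[1 − (3r1 + 2r2 + r3)/6]
- Participant-by-device variance kσ² adds kσ² to the true variance but only kσ²/3 to the reported one.

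R is the square root of reported over true variance. One-sided error at −1.5 g is 1 − Φ(1.96R). Power at N is Φ(2.802√(N/38) − 1.96R).

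| Assumed pattern | True/σ² | Reported/σ² | R | One-sided error | Power at 38 |
|---|---|---|---|---|---|
| Equal correlation | 1.000 | 1.000 | 1.00 | 2.5% | 80% |
| AR(1) 0.2 | 0.736 | 0.885 | 1.097 | 1.6% | 74% |
| AR(1) 0.5 | 0.4375 | 0.646 | 1.215 | 0.9% | 66% |
| AR(1) 0.7 | 0.2685 | 0.4295 | 1.265 | 0.7% | 63% |
| AR(1) −0.2 | 1.344 | 1.088 | 0.900 | 3.9% | 85% |
| Device variance k = 0.5 | 1.500 | 1.167 | 0.882 | 4.2% | 86% |
| AR(1) 0.5 and k = 0.5 | 0.9375 | 0.8125 | 0.931 | 3.4% | 84% |

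Power above 80% in the last three rows is not a gain. It comes from an interval that is too short.

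**At the target of 42.** The formula gives 79%, 71% and 68% at AR(1) 0.2, 0.5 and 0.7. Simulation with t-based limits gives 78%, 70% and 67%, against about 82% for the per-participant contrast adjusted for sequence. That contrast kept one-sided error at about 2.5% in every scenario simulated. Under true equal correlation the two analyses had about 83% and 82% power.

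**Individual recovery slopes.** If each participant has a separate linear slope with variance v, the true contrast variance gains v and the reported one gains 5v/3. With session SD 2 g and slope SD 1 g/day, R = √[(4 + 1.667)/(4 + 1)] = 1.065. With slope SD 2 g/day, R = √[(4 + 6.667)/(4 + 4)] = 1.155.

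**Missing day term.** Under equal correlation at N = 38, a common decline of 1 or 2 g/day left out of the model lowered simulated power from 79% to 75% and 61%. The figures in the table contain no such trend.

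**The case against.** The strongest objection is that the article does not state equal correlation. It is silent on the residual covariance, and a condensed protocol article may leave that to the analysis plan. This stands in part: an analysis plan could add a structure, and the point is easily closed there. But the article is not silent on the model. It names the fixed and random effects and takes the deciding interval from them, and fitted as named the model imposes equal correlation.

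A reader might also infer a stronger claim, that the interval is too wide and the trial loses power. The documents do not support it. Rapid change in the illness does not establish positive correlation between neighbouring days, and a gradual decline is a trend in the mean, not a covariance. With no washout, one day's clearance could lower the next day's yield. Even with AR(1) 0.5, a device-response variance of half the residual variance turns the interval from too wide to too narrow. The opposite claim, that the trial will declare non-inferiority too easily, has no better support.

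Finally, the power loss is relative. Its size depends on scaling the variance so that a correct interval has 80% power at 38. With a smaller true variance, power could stay above 80% even when the interval is too wide. That is correct, and it is why the power figures are conditional. The ratios R and the error rates do not depend on that scaling.

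**Conclusion.** The point holds in a conditional form. As stated, the primary model gives a valid non-inferiority interval only under equal correlation across the four days, and the protocol's own account of the illness and the alternating layout give reason to doubt that.

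- With assumed AR(1) correlation of 0.2 to 0.7, the standard error is about 10 to 26% too large, and power at 42 is 78 to 67% instead of about 82%.
- With assumed device-response variance of half the residual variance, or AR(1) −0.2, the interval is 10 to 12% too narrow and one-sided error is about 4% instead of 2.5%.

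Which applies cannot be told from the documents, and the mechanisms may partly cancel. For a non-inferiority claim the second error is the more serious. The uncertainty about direction is itself a reason to choose an analysis that does not depend on the assumption.

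**What to change.** In Statistical analysis, take the non-inferiority interval from a model with treatment and day as fixed effects, an unstructured within-participant covariance over Days 1 to 4, and Kenward-Roger degrees of freedom. If all four sessions are complete, a simpler valid alternative is the per-participant contrast (mean of the two NNPO days minus mean of the two OPEP days), adjusted for sequence. Name one of them as primary.

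The unstructured form covers both directions. Device-response variation adds the same day-by-day pattern in both sequences, so it is absorbed together with any serial correlation.

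AR(1) alone should not be used, because one lag parameter cannot separate the two sources. With AR(1) 0.5 and device-response variance of 0.25 times the residual variance, large-sample one-sided error is 2.2% under the stated model but 3.6% under a random intercept plus AR(1). With device-response variance of 0.5 times, it goes from 3.4% to 4.1%.

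The cost is a sentence or two of analysis text and about one percentage point of power if equal correlation is in fact true. No change to data collection is needed.
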